While we have confirmed others' results that a gender gap may exist at various points during the research process, exploration of gender bias at the point of manuscript evaluation by editors of academic journals is warranted. In a preliminary analysis of all original articles submitted between July and December 2017 to the journal *Clinical Microbiology and Infection*, we found—paradoxically—that women first authors, though fewer in number, had significantly higher acceptance for publication than their male counterparts (45% versus 27%,  $p=0.003$ ); the editor's gender had no effect on rates of acceptance. This unexpected result obtained in a single journal specializing in infectious diseases and clinical microbiology from original articles submitted over a six-month period is unlikely to be generalizable. Furthermore, gender bias should be assessed in multivariate analyses, independently of other study attributes known to be associated with chances of publication. It has, however, heightened our motivation to test the research hypothesis on a larger sample of journals from various medical domains.

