### **2.3.9. Statistical methods**

#### **2.3.9.1. Sample size**

As described above, we will consider an odds ratio of 0.85 for the acceptance for publication by first-author gender (0.85 for women versus men), to indicate the presence of gender bias. We assume a proportion of women first authors of 40% among cases and 44% among controls using  $OR=0.85$ . Taking into account a type-1 error at 5% (two-sided) with a study power of 90% and a correlation coefficient for exposure between matched controls and cases at 0.03 (to take into account some clustering at the journal level), this would require 2800 articles accepted and 2800 articles rejected after peer review. To take into account at least 20% of missing values among modelled variables, we will select a total of 3500 accepted and 3500 rejected manuscripts. We will randomly select an

equal number of articles per journal-year (20 cases and 20 controls) corresponding to a maximum of 160 cases and 160 controls for each journal. Currently, 23 journals have agreed to participate.

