#### **2.3.9.2. Statistical analyses**

Statistical analyses will be done by the postdoctorate under the supervision of [name]. We will present descriptive statistics for the proportions of women first authors that were: rejected without external review; sent for external peer review; rejected, accepted or invited to revise a manuscript after external peer review; and rejected and accepted after revision. To take into account clustering at the journal level, we will perform mixed-effects logistic regression to model the influence of the first author's gender on the odds of acceptance for publication, after adjustment for the confounders and covariates (cf. appendix 7) and using the journal as a random effect. We will perform the same logistic regression model to answer our secondary objectives to study the influence of corresponding-author gender or last-author gender on the acceptance for publication. To test whether the handling editor's gender or reviewers' gender modifies the association between first-author gender and the acceptance rate, we will include an interaction term between these two predictors. We will also test interactions of first author gender, respectively with the scope of the journal and with time on a yearly scale. Journals will be anonymised, therefore separate journal effects will not be presented when we publish the results but we will provide journal level data to individual journals upon request.

In the retrospective cohort, we will describe and compare, using Chi-2 tests, the proportion of women first authors for articles at the following points in the decision-making process: rejection without review; sent for peer review; rejected, accepted and sent for revision after peer review; and between articles rejected at any stage versus articles accepted for publication. To test whether the reasons for rejection mentioned in decision letters varies between men and women first (then corresponding and last) authors, we will include an interaction term between these two predictors in a mixed-effects logistic regression model with rejection as the dependent variable and journal as the random factor. All analyses will be performed using STATA 17.0 IC (StataCorp LP, College Station, TX, USA) and R software (version 4.0.5).

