## THE ATHENA STUDY: FIRST AUTHOR'S GENDER AND ACCEPTANCE FOR PUBLICATION

**Appendix 7.** Data extracted for the case-control study.

| Variables                                                  | Description                                                                                                                                                                                                                                          |
|------------------------------------------------------------|------------------------------------------------------------------------------------------------------------------------------------------------------------------------------------------------------------------------------------------------------|
| Unique ID of manuscript                                    | tracking number generated during submission process                                                                                                                                                                                                  |
| Journal identifier                                         | ##                                                                                                                                                                                                                                                   |
| Scope of the journal                                       | 1= infectious diseases journal 2= family medicine 3=internal medicine
4=others                                                                                                                                                                    |
| Date of submission                                         | __ / __ / ____                                                                                                                                                                                                                                       |
| Handling editor's gender                                   | 0=man, 1=woman                                                                                                                                                                                                                                       |

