## THE ATHENA STUDY: FIRST AUTHOR'S GENDER AND ACCEPTANCE FOR PUBLICATION

**Appendix 8.** Case-report form for the retrospective cohort study.

| Variables                                                    | Description                                                                                                                                                                                                                                 |
|--------------------------------------------------------------|---------------------------------------------------------------------------------------------------------------------------------------------------------------------------------------------------------------------------------------------|
| Unique ID of manuscript                                      | tracking number generated during submission process                                                                                                                                                                                         |
| Journal identifier                                           | ##                                                                                                                                                                                                                                          |
| Scope of the journal                                         | 1= general medical journal 2= specialist journal                                                                                                                                                                                            |
| Date of submission                                           | __ / __ / ____                                                                                                                                                                                                                              |
| Study design                                                 | 1=randomised-controlled trial, 2= cohort, prospective, 3=cohort retrospective, 4=cross-sectional, 5=case-control, 6=case reports or case series, 7=systematic review without meta-analysis, 8=systematic review and meta-analysis, 9= other |

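### The gender-by-scope interaction compares 23 journals, but the stated model lets no gender effect vary by journal, so its false-positive rate exceeds 5% to the extent that journals of the same scope differ

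*Protocol*

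**What the plan says.** Protocol 2.3.9.2 sets out the model: "To take into account clustering at the journal level, we will perform mixed-effects logistic regression", with adjustment for covariates and "using the journal as a random effect". It then adds the test at issue: "We will also test interactions of first author gender, respectively with the scope of the journal and with time on a yearly scale". No journal-specific gender effect is mentioned, and no reference distribution is given for the interaction.

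Scope is recorded as one code per journal. Appendix 7 (case-control study) has four codes: "1= infectious diseases journal 2= family medicine 3=internal medicine", and a fourth for all other journals. Appendix 8 (cohort) has two: "1= general medical journal 2= specialist journal".

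On the number of units, section 2.3.9.1 says: "Currently, 23 journals have agreed to participate". Sampling is 20 cases and 20 controls per journal-year, "corresponding to a maximum of 160 cases and 160 controls for each journal". The protocol does not say how far the gender effect varies between journals or which journal belongs to which scope class. Section 2.3.9.2 also withholds journal-specific results from publication.

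**The concern.** Because scope does not vary within a journal, more articles from the same journal sharpen the estimate of that journal's gender effect. They add no further journals of that scope. If the effect differs between journals of the same scope, that variation belongs in the error term of the scope contrast. A random intercept allows the level of acceptance to differ by journal, but not the gender effect, so the variation is left out.

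At stake is a statement that gender bias depends on specialty when the signal comes from one or two journals. Readers could not check this, since journal-level results will not be shown. The year interaction in the same sentence is not part of this point, because year varies within journals.

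**Working it through.** **Plan's own figure.** There is none for this interaction. The sample size in 2.3.9.1 concerns the main gender effect. It fixes the amount of data per journal: 160 + 160 articles at most, or 160 × 0.80 = 128 + 128 after the planned 20% loss.

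**Units.** There are 23 journals. Between-journal degrees of freedom for the scope term are 23 − 4 = 19 with the Appendix 7 coding and 23 − 2 = 21 with the Appendix 8 coding.

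**What the random intercept absorbs.** Equal numbers of cases and controls are drawn per journal-year, so about half of each journal's articles are accepted by design. Almost no intercept variance is left. The correlation of 0.03 in 2.3.9.1 concerns the exposure, that is, the share of women. It does not describe variation in the gender effect.

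**Analytic size of the problem.** Take 40% women among cases and 44% among controls (2.3.9.1). With n cases and n controls in a journal, the variance of its log odds ratio is

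v = (1/n) × (1/0.40 + 1/0.60 + 1/0.44 + 1/0.56)

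- n = 160: v = 0.0514 (SE 0.227)
- n = 128: v = 0.0643 (SE 0.253)

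Let tau be the SD of the true log odds ratio between journals of the same scope. The common-slope model uses v where v + tau² is needed, so its test statistic is inflated by 1 + tau²/v. For tau = 0.2 and n = 160 this is 1 + 0.04/0.0514 = 1.78. A nominal 5% test then rejects in 14% of studies with 1 df (two classes) and 22% with 3 df (four classes). At tau = 0 the factor is 1 and the level is 5%.

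**Simulation, no true scope effect.** A random-intercept logistic model with a likelihood-ratio test of gender by scope was run 1500 times per setting. The Monte Carlo standard error is about 0.6 percentage points at 5% and 1.2 at 35%. Assumptions:

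- 21 journals with eight years, one with four and one with three, from the start dates in 2.3.8. This makes 175 journal-years against the stated 172, which is immaterial here.
- The share of women among controls varies by journal with SD 0.086, which is √(0.03 × 0.44 × 0.56).
- Journals split 5/18 (two classes) or 3/2/4/14 (four classes). This allocation is assumed.
- tau is assumed and varied from 0 to 0.3.

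| Scope classes | Articles per journal-year | tau 0 | 0.1 | 0.2 | 0.3 |
|---|---|---|---|---|---|
| Two | 20 + 20 | 4.1% | 5.6% | 11.5% | 19.8% |
| Two | 16 + 16 | 5.2% | 6.2% | 10.1% | 17.3% |
| Four | 20 + 20 | 4.3% | 7.7% | 17.7% | 35.5% |
| Four | 16 + 16 | 4.6% | 6.9% | 15.2% | 32.0% |

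The analytic values lie somewhat above these for tau from 0.1 to 0.3 and show the same pattern. A further simulation, with three classes allocated by journal title and an article-level 2-df test, gave 7%, 16% and 29% at tau 0.1, 0.2 and 0.3 with 128 + 128 articles per full-length journal, and 8%, 18% and 33% with 160 + 160.

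**Same data, journal as the unit.** A meta-regression of journal log odds ratios on scope, with residual between-journal variance and an F test, rejected in 1.6% to 4.5% across all settings in the table. The three-class version gave 4.9% to 5.4%.

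**The case against.** **The structure may be left to the SAP.** A random effect for journal does not exclude a random slope, and an SAP that is not shown could specify one. This stands as a caution about the reading. But the protocol does name the model and the test, its stated purpose is clustering, and it mentions no slope. Read naturally, the two do not fit a journal-level attribute.

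**Articles are not treated as independent.** A reader might infer that clustering is ignored altogether. It is not: a journal random effect is planned. What is missing is a gender effect that can vary by journal.

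**The excess is not established.** A reader might infer a false-positive rate well above 5%. The documents do not support this, because they give no tau. The test is nominal at tau = 0 and only slightly off at 0.1.

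**The pilot does not set the size.** Section 2.2 reports acceptance of 45% for women against 27% for men at one infectious-disease journal, an odds ratio of (0.45/0.55)/(0.27/0.73) = 2.21. It is tempting to set this against 0.85 elsewhere. If one of three infectious-disease journals had 2.21 and all others 0.85, a common-slope test would declare a scope effect in 33% to 59% of runs. That is a constructed case. The pilot is unadjusted, covers six months, and includes all submitted original articles, whereas 0.85 applies to peer-reviewed articles. The protocol itself doubts that it generalises. It makes some variation plausible and no more.

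**The stakes are limited.** The scope interaction is not among the objectives in 1.2 or 2.3.3, and no sample size or decision rule rests on it. This stands.

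**Conclusion.** The point holds in conditional form. The gender-by-scope test is a comparison between 23 journals. As naturally read, the stated model leaves between-journal variation in the gender effect out of its error term. The false-positive rate is nominal without such variation. It is about 6–8%, 10–18% and 17–36% for an assumed SD of the log odds ratio of 0.1, 0.2 and 0.3. The upper ends belong to the four-class coding, which is the one attached to the case-control study. The SD and the allocation of journals to classes are assumptions, and the reading of the journal term as an intercept is the natural one but not the only one possible.

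This is a secondary test. A reader might infer that the confidence interval of the primary odds ratio is also at fault, but nothing in this point bears on it.

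**What to change.** Add to 2.3.9.2 that, for the gender-by-scope interaction, either:

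- the model includes a journal-level random slope for first-author gender, and the scope term is referred to a t or F distribution with denominator degrees of freedom equal to journals minus scope classes (19 for the four codes of Appendix 7); or
- the journal-specific log odds ratios are regressed on scope in a random-effects meta-regression with the Knapp-Hartung adjustment.

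Report the number of journals in each scope class beside the result. This can be done without naming journals. Say of any class with only two or three journals that it cannot separate specialty from the individual journals. This statement is needed because the journal-level test reduces the influence of one atypical journal but does not remove it: in the constructed case above it still rejected in 10% to 36% of runs.

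The cost is a sentence or two of text and a few lines of code. The interval for the scope contrast becomes wider, and the test can be conservative when journals hardly differ (1.6% to 3.4% at tau = 0 in the runs tabulated). That reflects the number of journals available.

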### **1.2. Overall objectives and specific aims**

Our primary objective is to study the association of first authors' gender with acceptance for publication of original research articles sent for peer review. Our secondary aims are also 1) to study the association of last authors' gender with acceptance for publication of original research articles sent for peer review; 2) to examine the existence of a geographical bias during the editorial decision-making process; 4) to assess the existence of an independent gender bias against first authors at key decision points (first and last decision by editors, peer reviewers' score and recommendations) in the editorial decision-making process from initial submission to final decision.

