### 2.3.3. Objectives

Our **primary objective** is to evaluate the influence of first-author gender on acceptance rates of original articles submitted to leading medical journals that were sent for peer review.

Our **secondary objectives** are: 1) to study the influence of corresponding-author gender and last-author gender on acceptance for publication; 2) to test whether the editor's or associate editor's (see glossary) gender modifies the influence of author gender on acceptance for publication; 3) to determine whether the influence of author gender on acceptance for publication varies over an eight-year period; 4) to determine the proportion of women first authors at each stage of the editorial decision-making process; 5) to possibly explore whether the reasons for manuscript rejection differ between women and men first, last and corresponding authors.

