#### **2.3.4. Study design**

We will conduct a case-control study (main study design) nested in a retrospective cohort of original articles submitted to leading medical journals of various specialties during an eight-year period (January 2012 through December 2019). The cases will be a randomly selected sample of original research articles sent for peer review. Due to low acceptance rates in some of the selected journals, we will conduct a stratified case-control study on the journal.

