#### **2.3.8.1.2. Extraction for the retrospective cohort study**

Regarding variables for the retrospective cohort, most variables will be directly exported from the journal systems in plain text (CSV or XLS). These variables will include the date of submission, the article's first decision and last decision, the authors' the countries of affiliation, and the journal identifier (case report form; see appendix 8). We will complete data extraction (for study design, statistical significance of main result, etc.) from the abstracts of the manuscripts by using text mining techniques elaborated by our project partner.

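### The cohort's Chi-2 tests name no journal or year, so they cannot show an independent gender bias at the desk decision, the first decision after review or overall acceptance

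*Protocol*

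**What the plan says.** For the cohort, Protocol 2.3.9.2 says: "we will describe and compare, using Chi-2 tests, the proportion of women first authors for articles at the following points in the decision-making process". The points listed are rejection without review, sending for review, the outcomes after review, and rejection at any stage against acceptance. The sentence mentions no journal stratum, random effect, calendar year or covariate.

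The objective behind these tests is worded in two ways:

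- Section 1.2, in the aim numbered 4: "to assess the existence of an independent gender bias against first authors at key decision points". It covers the first and last editorial decisions and the reviewers' scores and recommendations, from submission to final decision.
- Section 2.3.3, in the fourth secondary objective: "to determine the proportion of women first authors at each stage of the editorial decision-making process".

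The preceding paragraph of 2.3.9.2 does deal with journals: "To take into account clustering at the journal level, we will perform mixed-effects logistic regression to model the influence of the first author's gender". That model takes its covariates from Appendix 7, which is the case-control variable list. Under 2.3.7.1 the case-control study contains only manuscripts accepted or rejected after peer review.

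On differences between journals, 2.3.4 gives as its reason for stratifying the case-control sample: "Due to low acceptance rates in some of the selected journals". Section 2.3.5.1 says that the journals cover various specialties.

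**The concern.** A Chi-2 test on manuscripts combined over 23 journals and eight years compares women and men who did not submit to the same journals in the same proportions. If journals with low acceptance also receive a larger or smaller share of manuscripts led by women, the crude table mixes that pattern with any effect of gender on the decision. The same holds for calendar year, and 2.1 reports that women's first authorship rose between 2000 and 2015. The crude test also ignores clustering by journal.

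The desk decision matters most, because the case-control study cannot see it. Section 1.4 says that if no bias is found in editors' and reviewers' decisions, the imbalance will be attributed more to earlier steps, and 2.5.2 foresees shifting resources on that basis. A crude null at the desk stage would not support that conclusion, and a crude gap would not support the opposite one.

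**Working it through.** **Which decisions get an adjusted analysis**

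| Decision | Planned analysis | Journal in the analysis? |
|---|---|---|
| Accepted or rejected after peer review | Case-control mixed logistic model | Yes, random effect |
| Desk rejection or sent for review | Cohort Chi-2 | Not named |
| First decision after review (reject, accept, revise) | Cohort Chi-2 | Not named |
| Rejected at any stage or accepted | Cohort Chi-2 | Not named |
| Reviewers' scores and recommendations | None; no field in Appendix 7 or 8 | – |

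The other mixed model in the cohort paragraph concerns reasons for rejection. It does not estimate a gender effect at each stage.

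**How far a crude table can move**

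The plan has no figure of its own to reproduce here. It gives no journal-specific acceptance rates or women's shares and no cohort size. All inputs below are therefore assumptions: two journals of equal size, with women's share w and men's acceptance a in each.

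- Women's acceptance in a journal has odds OR × a/(1 − a), where OR is the true within-journal odds ratio.
- Pooled acceptance of women = Σ(w × women's acceptance) / Σw. For men it is Σ((1 − w) × a) / Σ(1 − w).
- Pooled OR = odds of acceptance for women / odds for men.

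Example with no gender effect, w = 48% and 35%, a = 10% and 40%:

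- Women: (48 × 0.10 + 35 × 0.40) / 83 = 18.8/83 = 22.7%.
- Men: (52 × 0.10 + 65 × 0.40) / 117 = 31.2/117 = 26.7%.
- Pooled OR = (18.8/64.2) / (31.2/85.8) = 0.805.

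| True OR | Women's share | Men's acceptance | Pooled women / men | Pooled OR |
|---|---|---|---|---|
| 1.00 | 48% / 35% | 10% / 40% | 22.7% / 26.7% | 0.805 |
| 1.00 | 30% / 50% | 30% / 15% | 20.6% / 23.8% | 0.834 |
| 1.00 | 35% / 45% | 30% / 10% | 18.8% / 20.8% | 0.877 |
| 1.00 | 38% / 42% | 22% / 15% | 18.3% / 18.6% | 0.981 |
| 1.00 | 38% / 48% | 15% / 35% | 26.2% / 24.1% | 1.115 |
| 1.00 | 35% / 48% | 10% / 40% | 27.3% / 23.3% | 1.237 |
| 0.85 | 50% / 30% | 30% / 15% | 21.6% / 21.3% | 1.020 |
| 0.85 | 45% / 35% | 30% / 10% | 18.8% / 19.2% | 0.976 |
| 0.85 | 42% / 38% | 22% / 15% | 16.3% / 18.4% | 0.868 |

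With an assumed 10,000 submissions per journal, the crude Chi-2 gives:

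- for the pooled ORs of 0.834, 0.877 and 0.981 under no true effect, p = 2 × 10⁻⁷, 0.0003 and 0.60;
- for the three rows with a true OR of 0.85, in table order, p = 0.58, 0.51 and 0.0002.

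In these same six cases, the Mantel-Haenszel OR stratified by journal returns 1.00 in the first three and 0.85 in the last three (p < 0.0001 in each of the last three).

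**The case against.** The best defence is that the stage comparison is secondary and descriptive. Section 2.3.3 asks for proportions, and crude proportions with a Chi-2 test answer that. This stands in part, since dropping the claim of independence from 1.2 and labelling the tests as crude would remove the contradiction. It does not rescue the plan as written, because 1.2 does claim independence and 2.3.9.2 goes beyond description to hypothesis tests.

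It can also be said that the text never uses the word pooled. That is an inference, but a plain Chi-2 test with no stratum named is a crude test, and the preceding paragraph says so when journal clustering is handled.

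Four stronger readings are tempting and are not supported:

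- That the aim goes wholly unanswered. Final acceptance after review has an adjusted analysis in the case-control study.
- That the plan breaks a rule of its own in 2.2, "gender bias should be assessed in multivariate analyses, independently of other study attributes known to be associated with chances of publication". That remark comments on a preliminary single-journal result, and the primary model honours it. It is a relevant standard, but not a stated requirement for every stage table.
- That even a small spurious gap is bound to be significant. No cohort size is stated, and the mild case above gives p = 0.60 with 20,000 submissions.
- That a distortion of the size of 0.85 is to be expected. Two journals are always perfectly aligned; across 23 the alignment may be much weaker. The 0.85 is also the case-control design effect in 2.3.9.1, not a cohort threshold, and serves here only as a yardstick.

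**Conclusion.** The point holds for three comparisons: the desk decision, the first decision after review, and overall acceptance. For these the protocol itself fixes an unadjusted test, so this is not detail left to a later analysis plan, and such a test cannot support a statement about independent bias.

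The size of the distortion is unknown in advance. Under the assumed inputs, a true odds ratio of 1.00 can appear as anything from about 0.81 to 1.24, and a true 0.85 as 0.87 to 1.02. With small differences between journals the distortion is slight (0.98 for 1.00, 0.87 for 0.85). These figures show what is possible, not what is likely. They rest on women's share and acceptance varying together across journals. The protocol supports variation in acceptance only qualitatively, and it gives no journal-level women's shares.

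Secondary aims are affected. The primary case-control analysis is not. The missing reviewer scores and recommendations are a separate gap in data and analysis under the same aim.

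**What to change.** 1. Keep the crude proportions at each stage as description.
2. Replace the Chi-2 tests with one estimate per decision, among manuscripts that reach it: sent for review among all submitted; first decision among those reviewed; accepted among all submitted. Use a Mantel-Haenszel odds ratio stratified by journal and submission year, or logistic regression conditional on journal and year. A journal random intercept alone may leave some between-journal confounding.
3. If covariates are added, use only manuscript attributes fixed at submission. Appendix 8 also lists numbers of reviewers and revisions and other reviewer variables. These arise after the desk decision and should not be adjusted for there.
4. Reconcile 1.2 and 2.3.3 so that the stage objective is either descriptive or a claim of independent association.
5. Add reviewers' scores and recommendations to the data lists with an analysis, or delete them from the aim in 1.2.

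The cost of item 2 is small. Journal identifier and submission date are in Appendix 8, and 2.3.8.1.2 has the first and last decisions exported from the journal systems. Item 3 costs more, because attributes such as study design must still be drawn "from the abstracts of the manuscripts by using text mining techniques elaborated by our project partner", and their completeness is not shown. The journal-year analysis does not depend on them.
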